#### 2.5.2. Fitness Tests

The fitness tests will be performed with a protocol similar to the one described in the dissertation of Pihlainen [29]. They will include endurance and muscle fitness testing. All fitness tests, protocols, and techniques will be standardized according to the Fitness Test Manual of the Training Division. The annual fitness tests adhere to the regular protocol in the Finnish Defence Forces: professional soldiers are required to take the tests annually as a prerequisite to field training, and to encourage exercise during working hours; civilian workers are required to take the tests to obtain permission to exercise during their working hours. [10,30]. The tests will be supervised and demonstrated by instructors.

The FDF has three separate tests to evaluate aerobic capacity. Maximal aerobic capacity will be assessed by a 12 min running test [31], a cycle ergometer test [32], or a UKK 2 km walking test [33]. Each participant will select one of those three tests, depending on her/his working status and age. If a participant is unable to perform the 12 min running test, he or she can select either the cycle ergometer test or the UKK 2 km walking test. Each participant will perform only one aerobic test.

Participants will perform the strength and endurance tests on different days to avoid excess strain. Before the maximal test, participants will be asked about the following risk factors: whether there are any personal or close family members (i.e., siblings, parents, or children) who have had coronary disease (e.g., death due to severe cardiac disease, cardiac infarct, cardiac bypass, or assumed or known cardiac disease-related death of a person under 55 years of age); whether the participant has engaged in regular smoking or quit smoking within the previous six months, or had high blood pressure (systolic pressure ≥ 140 mmHg or diastolic pressure ≥ 90 mmHg), high cholesterol (total cholesterol over 5.2 mmol/L, HDL under 0.9 mmol/L or LDL over 3.4 mmol/L), an inactive lifestyle (office work and no regular exercise), high fasting glucose levels (fasting glucose ≥ 6.1), or a BMI of ≥30. If a participant reports two or more risk factors, he or she will be evaluated by a physician. The physician will decide if the maximal fitness test will be carried out. Before the 2 km walking test, the risk evaluation will not be necessary [30].

The 12 min running test will be conducted as a maximal test on an outdoor track during the summer, or in indoor hall during the winter. Participants will be encouraged to run with a maximal effort at a progressively increasing running speed. The test results will be recorded with an accuracy of 10 m [30,31].

A cycle ergometer test will be performed with an indoor cycle ergometer (Ergoline 800S, Ergoselect 100K, Ergoselect 200K, Bitz, Saksa) as a maximal test (for healthy soldiers) or submaximal test (for civilian workers) [34,35]. In the maximal test, a progressive protocol will be used with an initial power output of 50 W, increased by 25 W every 2 min until exhaustion. A participant’s exhaustion will be determined by one or both of the following criteria: (1) a decrease in pedaling frequency to below 60 rpm/min, and/or (2) the participant’s volitional cessation of pedaling. The heart rate of participants will be continuously recorded during the test, using heart rate monitors (Polar Electro, Kempele, Finland). The maximal aerobic capacity (VO_2_max) will be indirectly determined according to the heart rate results. The intraclass correlation has been reported to be high for men with this method (ICC r = 0.82–0.94) [34].

In the UKK 2 km walking test, a 2 km distance will be covered at the maximum speed while the heart rate and performance time are measured. The UKK 2 km test will be used only for civilian workers. The test will be conducted on an outdoor track during the summer and on in an indoor hall during the winter. The time will be recorded to an accuracy of one second, and the participant’s heart rate will be measured at the end of the test. The VO2max will be determined indirectly according to these results [33].

The FDF has three different muscle fitness tests, including standing long-jumps (SLJ), repeated (1 min) sit-ups, and push-ups. The SLJ will be used to assess the power of the participant’s lower extremities. The dynamic muscle endurance capacity of the participant’s trunk and upper extremities will be assessed by sit-ups and push-ups. Together, these three parts of the muscle strength test will demonstrate participants’ overall muscle fitness.

Before the SLJ, participants will be instructed on the proper technique. Three test attempts will be allowed, and the jumps will be performed on a 10 mm thick rubber mattress. The best attempt (i.e., the longest distance from the starting line to the landing point) will be selected for further analysis [36].

Participants will be also shown the proper techniques for both sit-ups and push-ups, and they will be informed that incorrect repetitions will not be accepted for final analysis. The sit-up test will start and end in a lying-down position. In the starting position, participants will lie on their backs as the knees are bent at a 90° angle, with the elbows pointing upwards and the fingers interlocked behind the head. An assistant will support the ankles to keep the heels in contact with the floor during the test. From the starting position, the upper body will be raised forward by the trunk muscles until the elbows reach knee level. One repetition will be completed when the body is lowered and the bottom of the shoulder blades touch the ground. The test result will be expressed as the number of consecutive repetitions in 60 s [37,38].

The push-up repetitions will be counted for a minute, and only consecutive correctly performed repetitions will be accepted for analysis. The correct position for the push-up test will be determined as participants lie on the floor in a front-leaning rest position, with feet parallel at shoulder width and hands positioned so that the thumbs reach the shoulders as the other fingers point forward. The starting position will progress from this position by extending the arms straight while keeping the body in a straight line from the shoulders to the ankles as the knee and hip angles remain steady throughout the test. One repetition will be counted when the torso is lowered by bending the elbows until the upper arms are parallel to the floor and returned to the starting position by extending the arms [38,39].

#### 2.5.3. Body Composition

The body composition measurements of participants will be performed as discussed earlier [38]. The waist circumference measurement, body mass index (BMI), and fat tissue percentage (FAT%) will be used to assess body composition. Body mass (BM) and FAT% will be measured by using the segmental multifrequency bioimpedance analysis assessment (BIA) (InBody 720, Biospace Co Ltd., Seoul, Korea).

The BIA estimates of body composition have been shown to correlate highly with the dual-energy X-ray absorptiometry (DXA) method (r = 0.82–0.95) [40]. The waist circumference of participants will be measured with a tape measure at the level of the iliac crest after exhaling.

Body composition measurement is sensitive to fluid changes in the body. To standardize fluid composition, the measurements will be performed before noon, and participants will be instructed to have fasted for 2 h, avoided alcohol consumption and excess physical strain for 12 h, and empty their bladders before the examination.

#### 2.5.4. Blood Samples and Analyses

Blood samples, for analyzing the health status of participants, will be collected into serum tubes (Venosafe Gel + Clot activator tubes, Terumo Medical Co., Leuven, Belgium) by a qualified laboratory technician during every measurement after a 12 h fast between 07:00 and 09:00. The samples will be centrifuged with 2000× *g* (Heraeus Megafuge 1.0 R, Thermo Scientific, Karlsruhe, Germany) for 10 min at a temperature of +4 °C. The serum will be stored at −80 °C until analysis.

Fasting glucose (GLUC), haemoglobin A1c (HbA1c), and serum insulin will be determined to detect imbalances in glucose metabolism [41,42]. Total cholesterol, high-density lipoprotein (HDL), low-density lipoprotein (LDL), oxidated low-density lipoprotein (ox-LDL), and oxidated high-density lipoprotein (ox-HDL) will be measured to observe body lipid status [43,44,45,46,47]. Alanine transaminase (ALAT), gamma-glutamyl transferase (GT), and carbohydrate-deficient transferrin (CDT) will be measured to evaluate liver function and the possibility of fatty liver disease [48,49,50]. Salivary alpha-amylase will be analyzed as an indicator of elevated stress levels [51].

Plasma glucose (GLUC), serum high-density lipoprotein (HDL), and triglycerides (TG) will be analyzed using a Konelab 20 XTi-device (Thermo Electron Co., Vantaa, Finland), and an isolated LDL fraction will be used for the direct measurement of LDL-cholesterol (CHOD-PAP method). The sensitivity for GLUC is 0.1 mmol/L, and the intra- and inter-assay coefficients of variance are 1.0 and 2.0%, respectively. The ranges for the CHOL, TG, HDL, and LDL assays varies from 0.1–15, 0.09–11, 0.04–2.84, and 0.3–8.9 mmol/L, respectively. Intra- and inter-assay coefficients of variance are 1.1% and 2.1% for CHOL, 1.0% and 3.8% for TG, 3.4% and 3.9% for LDL, and 0.5% and 7.6% for HDL, respectively.

The carbohydrate-deficient transferrin (CDT) will be analyzed using a Capillarys 2 (Sebia Co., Lisses, France) device. The sensitivity for CDT is 0.35%, and the intra- and inter-assay coefficients of variance are 10.3 and 11.2%, respectively.

#### 2.5.5. Baseline and Control Accelerometer Measurements

UKK RM42 accelerometers [9] will be used during baseline and control measurements to analyze daily physical activity and quality of sleep. The accelerometers will be worn for two weeks: on the hip during waking hours and on the wrist during sleep. The aim is that the measurements taken in the second week should demonstrate more physical challenges than the measurements taken in the previous week (i.e., due to field training). Movement in water cannot be measured with the accelerometer. The UKK RM42 accelerometer data will be analyzed subsequently; participants will not receive immediate feedback on the measurements during the actual measurement weeks.

#### 2.5.6. Feedback from the Measurements

All participants will receive feedback from the measurements at different stages of the study. Immediate feedback from the body composition measurements will be provided during every measurement event. Results and feedback from the laboratory tests will be provided after the analyses, and participants will be advised to contact a physician if the test results indicate a need for further examinations or follow-ups. The feedback from the RM42 accelerometer measurements will be provided after the final measurements.

## 3. Results

### 3.1. Primary Outcomes

The primary outcome variables will include changes in accelerometer-measured physical activity, physical fitness test results, and days of sick leave absences. Changes in physical activity levels will be evaluated by comparing physical activity measurements at the baseline and after the intervention. Changes in fitness test results will be evaluated by fitness tests results (i.e., changes in maximal aerobic capacity, SLJ distance, and number of sit-ups and push-ups). Changes in sick leave absences will be evaluated by comparing the number of days of sick leave absences in the year prior to the intervention with the number of days of sick leave absences during the intervention, and with the number of days of sick leave absences one year after the intervention. In addition, each participant’s mean daily number of steps, increases in mean daily total time, increases in number of light physical activities and moderate-to-vigorous physical activities, and reductions in mean daily total time of sedentary behavior will be assessed via two weeks of accelerometer recordings of physical activity at the baseline, immediately after intervention, and six months after intervention.

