### 2.3. Power Calculation and Sample Size

Before the intervention begins, power calculations will be determined, based on the means and standard deviations of personal fitness indices and short sick leave absences (i.e., seven or fewer calendar days) of FDF personnel. According to the results of an endurance test and a muscle strength test, participants’ endurance and muscle strength indices will be determined, using age-dependent reference values. The fitness index will be calculated as an average of the endurance and muscle strength indices [10]. The calculations will be based on the assumption that sick leave absences would reduce as fitness indices increase by a certain amount, i.e., that sick leave absences will reduce by 0.35 days per year for professional soldiers and by 0.40 days per year for civilian workers. The fitness indices will be assumed to increase by 0.14 for male soldiers; 0.45 for female soldiers; 0.34 for male civilian workers; and 0.24 for female civilian workers. For the evaluation of physical fitness, an appropriate number of study participants is approximately 175 soldiers and 99 civilians. To evaluate sick leave absences, an appropriate number of participants is approximately 115 soldiers and 97 civilians (G*Power 3.1.9.2, Wilcoxon signed-rank test (matched pairs), correlation between groups assumption r = 0.80).

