### 2.4. Intervention

The intervention will use a technique involving an interactive accelerometer, smartphone application, telephone counselling, and daily physical activity recordings. The intervention will last six months, and measurements of the intervention participants will be performed at the baseline, immediately after the intervention, and six months after the intervention. The intervention procedure is described in Table 1.

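### Sick-leave days over a 12-month pre-period are compared with days over a 6-month intervention period, so the within-arm change is about -50% even with no effect

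*Protocol article*

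**What the plan says.** Section 3.1 (Primary Outcomes) lists "days of sick leave absences" among the primary outcome variables. The change is to be evaluated by comparing days "in the year prior to the intervention with the number of days of sick leave absences during the intervention", and then "with the number of days of sick leave absences one year after the intervention".

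Section 2.4 sets the length of the second window: "The intervention will last six months".

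Section 2.3 states the effect assumed for power on an annual scale: "sick leave absences will reduce by 0.35 days per year for professional soldiers and by 0.40 days per year for civilian workers". For this outcome it gives the size as follows: "an appropriate number of participants is approximately 115 soldiers and 97 civilians". The calculation there uses a matched-pairs signed-rank test.

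Section 3.6 plans general or generalised linear models, including repeated measures, both by follow-up time and between study groups. It adds an intention-to-treat comparison of the arms and a per-protocol analysis of completers. Section 3.4 judges effectiveness by the shift in the monitored parameters. The end of the Introduction says that effects are assessed by comparing changes between the two groups.

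**The concern.** The outcome is a count of days, and a count grows with the time over which it is taken. A year is set against half a year, and none of the sections above puts the two on a common base. Followed literally, the change from before to during is negative by construction in both arms.

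Several parts of the plan look at change over time rather than only at the difference between arms: the outcome definition itself, the effectiveness statement, the repeated-measures time effect and the per-protocol wording about completers. The paired test in the power calculation belongs to the same family if its pairs are before and after. Each could lead to a report that sick leave fell during the intervention when nothing had changed.

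A second consequence reaches the comparison of arms. A difference in half-year counts is not in the unit in which the planned effect is stated.

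**Working it through.** **Inputs from the protocol article**
- Pre-period: 12 months (3.1).
- Intervention period: 6 months (2.4).
- Planned effects: 0.35 days per year for soldiers and 0.40 for civilians (2.3).
- Numbers for sick leave: about 115 soldiers and 97 civilians (2.3).
- Allocation: 2:1 (2.2).
- Significance level: 0.05 (3.6).

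**Assumed, because the article gives no figure**
- Mean yearly sick leave m, taken over a range.
- Spread between people.
- Share s of the yearly days that falls in the six-month window.

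**The plan's own figure.** The article states no expected before-during change. Its sample sizes cannot be recomputed, since the standard deviations, power and sidedness are not given. They can be inverted with dz = (z_alpha + z_power) / sqrt(n × ARE), where ARE is the relative efficiency of the signed-rank test. For two-sided 0.05, power 0.80 and ARE 3/π = 0.955:
- Soldiers: dz = 2.802 / sqrt(115 × 0.955) = 0.267, so the SD of the paired difference is 0.35 / 0.267 = 1.31 days.
- Civilians: dz = 2.802 / sqrt(97 × 0.955) = 0.291, so the SD is 0.40 / 0.291 = 1.37 days.

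Over one- and two-sided tests, power 0.80 to 0.95 and ARE 0.864 to 1, the implied SD is about 1.0 to 1.5 days (soldiers) and 1.0 to 1.6 days (civilians). This describes the planning scale and does not bear on the window problem itself.

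**Change expected with no effect.** At a constant rate:

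E[during − before] = m × 6/12 − m = −m/2, which is −50% whatever the value of m.

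| Assumed m (days/year) | Expected in 6 months | Apparent change |
|---|---|---|
| 1 | 0.5 | −0.5 |
| 2 | 1.0 | −1.0 |
| 3 | 1.5 | −1.5 |
| 5 | 2.5 | −2.5 |

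The artefact exceeds the planned effect once m/2 > 0.35, that is m > 0.70 (soldiers), or m/2 > 0.40, that is m > 0.80 (civilians).

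**Seasonality.** If the half-year holds share s of the yearly days, the apparent change is s − 1: −60% at s = 0.40 and −40% at s = 0.60.

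**Effect on tests.** Simulation with no effect, 2,000 runs per setting. Each person's yearly rate is drawn from a gamma distribution (shape 1, mean m), with Poisson counts at the full rate before and half the rate during.

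| m | Within-group paired signed-rank, n = 115 | Between-arm t-test on change, 77 vs 38 |
|---|---|---|
| 1 | 99.0% | 5.9% |
| 2 | 100% | 5.8% |
| 3 | 100% | 6.1% |
| 5 | 100% | 5.4% |

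A separate within-arm run used 141 intervention participants (2/3 × (115 + 97) = 141). It rejected in 97% to 98% of runs at m = 0.7 and in 100% at m = 2, 3 and 5. With the half-year count annualised, rejection returned to 4% to 6%.

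**Scale of the between-arm difference.** If the effect is constant from the first day, six months show 0.35 × 6/12 = 0.175 days and 0.40 × 6/12 = 0.20 days.

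**The case against.** The strongest reply is that the trial is randomised and both arms are counted over the same windows. The Introduction and section 3.6 base the effect on the comparison of groups. The shift of −m/2 is expected in each arm and cancels in that contrast, and the between-arm column above, at 5% to 6%, bears this out. This stands. A reader might infer that an ineffective intervention would be declared to halve sick leave. The documents do not support that: the near-certain rejection belongs to within-arm or time-effect tests, not to the randomised comparison.

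Further points also stand in part:
- The rejection rates rest on an assumed mean and spread. The −50% does not depend on m, but it does assume a constant rate.
- The paired test appears only in section 2.3, and section 3.6 does not list it. A repeated-measures time effect, however, is within what section 3.6 plans.
- Section 2.3 bases its calculation on short absences of at most seven calendar days, while section 3.1 does not state that limit. Setting m/2 against 0.35 and 0.40 may therefore mix two measures, so the break-even values are only a guide.
- Seasonality is shared by arms followed at the same time and does not bias their comparison.
- The contrast with one year after has equal windows if it means a 12-month total.

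It can also be said that offsets and distributions belong in an analysis plan, which is not shown. That holds for the choice of model. It does not cover the outcome definition, because the article itself fixes both windows and the raw-count scale.

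**Conclusion.** The outcome definition is wrong as written and should be corrected, but the randomised test remains valid. On raw counts, the within-arm before-during change with no effect is about −50% in both arms at a constant absence rate, and −40% to −60% if the six months hold 60% to 40% of the yearly days. A within-group or time-effect test on those counts would almost always find a fall, under the assumed means and dispersion.

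The between-arm comparison of change keeps its type I error. What it loses is scale: the planned annual effects would show at about half their size, provided that the effect is constant from the start, which the article does not state.

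The year-after contrast is sound if it is a 12-month window. The wording could also be read as a point in time, so this needs stating.

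**What to change.** In section 3.1:
1. Put the windows on one time base. Either express sick leave as days per person-time (or enter log person-time as an offset in the generalised linear model already planned in section 3.6), or take the same six calendar months of the preceding year as the baseline for the intervention window. The second option also matches the season.
2. State that the comparison with one year after the intervention uses a 12-month window.
3. State that the conclusion on sick leave rests on the between-arm contrast, adjusted for the pre-period rate, and that changes within an arm are descriptive.

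A negative-binomial model would suit such counts, but that choice is optional and can be left to the analysis plan.

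The cost is a few sentences and a date cut of absence records that the outcome already requires. No new measurement or participant is needed.

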### 3.2. Secondary Outcomes

The secondary outcomes of the study will be a reduction in the experienced stress assessed by the questionnaire, improvement in the analyzed biomarker levels, reduced BMI, reduced FAT%, decreased waist circumference, and increased amounts of restful sleep when the baseline measurements are compared to measurements taken six months after the intervention.

### 3.3. Reach

Reach will be assessed by dividing the number of the study’s participants by the total number of personnel in the brigades from which the participants will be recruited. Representativeness will be assessed by comparing the baseline information (age, gender, work status) with information obtained from the FDF’s statement of human resources 2018 [52].

### 3.4. Effectiveness

Effectiveness will be assessed by evaluating the shift in the monitored parameters.

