Reduced physical activity levels increase the risk of metabolic diseases, cardiovascular diseases, and other diseases [1], resulting in increased human resources costs. In the military workplace, Kyröläinen et al. [12] reported that poor muscle fitness and endurance, as well as a high body mass index (BMI), are risk factors for productivity loss, causing additional costs for employers. In 2016, the FDF estimated that sick leave absences cost 35 million euros [13].

To maintain the required physical performance of its workers, the FDF has developed a set of guidelines. To activate workers, one measure in the guidelines is to offer the opportunity to exercise during work for two hours per week, if annual fitness tests are performed [10]. Positive results have previously been achieved using physical training during the workday, showing that these FDF guideline measurements are a step in the right direction [8,14,15,16].

A limited number of studies have been published concerning physical activity and its effects on health in military populations. Additional actions are needed to promote the health and exercise habits of military workers. The present study aims to develop an intervention protocol to increase the physical activity of workers in military settings. Promising results have previously been demonstrated in interventions using accelerometers with online feedback and smartphone techniques in adolescents and adult civilians [17,18,19,20]. In the present study, the use of an interactive accelerometer with a smartphone application, telephone counselling, and the possibility of exercising for two hours a week during working hours to increase participants’ daily activities has been developed. The objectives of this study are to improve health outcomes, reduce stress, improve the quality of sleep, and improve the work performance of employees. The study also investigates whether increased physical activity during the intervention will improve physical fitness and lead to reduced sick leave absences. Thus, the hypothesis of the present study is that the intervention will result in increased daily physical activity, improved physical fitness, health promotion, and reduce sick leave absences. Comparing the changes in the measured parameters between the intervention and control groups will enable the effects of the intervention to be assessed.

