### 2.5. Measurements

All participants will be subject to baseline measurements at the beginning of the study, and similar measurements at the end of the study. Following the intervention, the intervention group participants will again be subject to all these measurements to observe the effects of the intervention. The control group participants will be subject to physical activity measurements via an RM42 accelerometer for two weeks, to examine whether any changes in their physical activities have taken place due to participation in the study, even without taking part in the intervention.

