### 3.6. Statistical Analysis

The continuous distributions will be described using means with standard deviations; regarding categorical data, the number of cases with percentages will be used. Differences between the intervention group and the control group will be tested using an independent samples *t*-test, a Pearson Chi-Square test, or a Fisher’s Exact test. Regression analyses will be used to evaluate the role of physical activity in the changes to physical fitness and the number of sick leave days. Changes in physical fitness and the number of days of sick leave, according to follow-up times and for comparison of the study groups, will be analyzed using general/generalized linear models (univariate, multivariate, and repeated measures) and regression analyses. The drop-out rate can be determined by comparing the number of participants attending baseline measurements to the number of participants attending follow-up measurements. Intention-to-treat analysis will be used to compare changes induced by the implemented intervention of the treatment groups, including all participants as originally allocated after randomization. In addition, a per-protocol analysis will be used to compare changes in the intervention participants who completed the treatment originally allocated. P-values under 0.05 are considered statistically significant. IBM SPSS Statistics version 26.0 for Windows (SPSS Inc., Chicago, IL, USA) was used for statistical analyses.

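### No sentence makes the between-arm difference in change the contrast that decides effectiveness, and several sections word the effect as a before-after shift

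*Protocol article*

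**What the plan says.** Two statements in the protocol article tie the effect to the comparison of the arms. The introduction says: "Comparing the changes in the measured parameters between the intervention and control groups will enable the effects of the intervention to be assessed". Section 3.6 says: "Intention-to-treat analysis will be used to compare changes induced by the implemented intervention of the treatment groups", in all participants as allocated. It also lists an independent-samples test between the groups and linear models for comparing them.

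Other statements describe the effect, or the outcome, without the control arm:

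- Section 2.5, on the visit after the intervention: "the intervention group participants will again be subject to all these measurements to observe the effects of the intervention". At that visit controls repeat only the RM42 accelerometry.
- Section 3.1, physical activity: "Changes in physical activity levels will be evaluated by comparing physical activity measurements at the baseline and after the intervention".
- Section 3.1, sick leave: "comparing the number of days of sick leave absences in the year prior to the intervention with the number of days of sick leave absences". Two later counts are meant, one from the intervention period and one from a year afterwards.
- Section 3.2: secondary outcomes are worded as improvements from baseline to six months after the intervention.
- Section 3.4, in full: "Effectiveness will be assessed by evaluating the shift in the monitored parameters".
- Section 3.6, per-protocol: "a per-protocol analysis will be used to compare changes in the intervention participants who completed the treatment originally allocated".

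Section 2.3 sizes the study with a paired test: "Wilcoxon signed-rank test (matched pairs), correlation between groups assumption r = 0.80".

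**The concern.** A before-after shift in the intervention arm and a difference in change between arms are different quantities and can disagree. Only the second uses the randomisation. The first also picks up whatever moves both arms.

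The article itself points to possible sources of such movement. The intervention lasts six months, so baseline and the next visit may fall in different seasons, and section 2.5.2 places the run and walk tests outdoors in summer and indoors in winter. Both arms receive body-composition results at every measurement and laboratory results after analysis (section 2.5.6). Fitness tests are repeated. Section 2.5 allows that controls' activity may change simply through taking part.

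If sections 2.5 and 3.4 and the per-protocol sentence were followed literally, such a shared trend would be credited to the intervention. For a null or borderline result, the conclusion would then depend on which contrast is reported.

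**Working it through.** **1. The wording, section by section.**

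| Place | Contrast worded | Control arm named? |
|---|---|---|
| Introduction | Change, intervention versus control | Yes |
| 3.6, intention-to-treat | Change, between treatment groups | Yes |
| 2.5, visit after the intervention | Intervention arm remeasured to see the effect | Only for accelerometry, in the next sentence |
| 3.1, activity and sick leave | Earlier versus later | No |
| 3.2 | Baseline versus six months after | No |
| 3.4 | The shift | No |
| 3.6, per-protocol | Change in intervention completers | No |

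Only the 2.5 sentence is explicitly within-arm as a statement about the effect. The others leave the comparator open, except the per-protocol sentence, which names intervention participants alone. No sentence ranks the contrasts.

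**2. Where a between-arm contrast can be computed (Table 1).** Both arms have accelerometry at baseline, after the intervention and six months later. Both have the questionnaire, body composition, fitness and laboratory tests at baseline and six months after the intervention, but only the intervention arm has them right after it. For those outcomes the only change available at that earlier visit is the intervention arm's own.

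**3. Size of the risk if the within-arm shift were used.**

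Inputs from the article: 175 soldiers and 99 civilians for fitness (section 2.3), two-thirds allocated to intervention (section 2.2), significance at 0.05 (section 3.6). The sample sizes themselves cannot be reproduced, because SDs, target power and sidedness are not stated; only the counts are used here.

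Treated: 175 × 2/3 ≈ 117; 99 × 2/3 = 66.

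Assumptions: no intervention effect; both arms drift favourably by the same amount d, in units of the SD of change; approximately normal changes; two-sided 5% test.

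Chance of a significant favourable paired result in the intervention arm = P(T > c), where T is noncentral t with n − 1 degrees of freedom and noncentrality d√n, and c is the 97.5% point of t with n − 1 degrees of freedom.

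| Treated n | c | d | d√n | Significantly favourable |
|---|---|---|---|---|
| 117 | 1.981 | 0.1 | 1.082 | 18.7% |
| 117 | 1.981 | 0.2 | 2.163 | 57.4% |
| 66 | 1.997 | 0.1 | 0.812 | 12.3% |
| 66 | 1.997 | 0.2 | 1.625 | 36.0% |

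With d = 0 the formula returns 2.5%, as it should.

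**4. The between-arm test under the same drift.** A common drift cancels in the difference of mean changes, so the favourable error rate stays at 2.5%. Simulation (10,000 runs per setting, 117 versus 58 and 66 versus 33, d from 0 to 0.5) gave 2.2% to 2.6%.

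**The case against.** The strongest reply is that the effect contrast is already stated where it counts, in the introduction and in the intention-to-treat sentence of section 3.6. Section 3.4 names no comparator rather than a within-arm one. The before-after sentences in 3.1 can be read as defining the change variable that 3.6 then compares between arms. Which test decides is commonly left to an analysis plan, which is not shown here. For activity, section 2.5 remeasures controls expressly to detect change without the intervention. Season cannot explain everything: the comparisons with six months after the intervention span about 12 months, so they fall in the same season, and the change of venue affects only the run and walk tests.

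Most of this stands. A reader might infer that sections 3.1 and 3.4 define a within-group estimand, or that the trial's type I error is not held at 5%. The article supports neither. The planned intention-to-treat comparison is protected against shared trends, and the inflation arises only if someone claims effectiveness from the within-arm shift.

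The reply does not remove the explicit wording in 2.5 or the intervention-only per-protocol analysis. Nor does it change the bare definition in 3.4, the one section headed Effectiveness. The paired sizing in 2.3 leans the same way, although the sample-size method is a separate matter. This is therefore more than detail left to another document: the published text gives an open reading of what counts as effective.

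**Conclusion.** The point holds as an ambiguity worth correcting. The article plans a sound between-arm comparison but never makes it decisive, and several sentences allow a before-after shift to be reported as the effect. Under that use, an ineffective intervention would look significantly favourable in about 19% to 57% of trials with 117 treated and 12% to 36% with 66 treated, for a common drift of 0.1 to 0.2 SD of change, against about 2.5% between arms.

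These figures rest on an assumed drift, for which the article gives no value, and on the within-arm test actually being used for the claim. They do not describe the error rate of the intention-to-treat analysis. The risk is most concrete for the outcomes measured only in the intervention arm right after the intervention, fitness among them, because no control change exists at that visit.

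**What to change.** Replace the sentence in section 3.4 with a definition along these lines: effectiveness is the between-arm difference (intervention minus control) in change from baseline, in all participants as randomised, at each visit where both arms are measured. Name the visits:

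- accelerometry: after the intervention and six months later;
- fitness, laboratory, body-composition and questionnaire outcomes: six months after the intervention, as Table 1 stands;
- sick leave: over periods of equal length or annualised, since a full prior year is otherwise set against a six-month intervention period.

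Align sections 2.5, 3.1 and 3.2 with this, and reword the per-protocol sentence so that it also compares the arms. Label within-arm changes, including the intervention-only measurements right after the intervention, as descriptive and without an effectiveness claim.

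The cost is wording; no new data are needed. The downside is that improvement within the intervention arm right after the six-month intervention can no longer be reported as an effect for outcomes not measured in controls at that visit.
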